# A cluster-randomized trial study on effectiveness of health education based intervention (HEBI) in improving flood disaster preparedness among community in Selangor, Malaysia: a study protocol

**DOI:** 10.1186/s12889-021-11719-3

**Published:** 2021-09-24

**Keywords:** Disaster preparedness, Health education, Health belief model, Community

## Abstract

**Background:**

Flood disaster preparedness among the community seldom received attention. Necessary intervention must be taken to prevent the problem. Health Education Based Intervention (HEBI) was developed following the Health Belief Model, particularly in improving flood disaster preparedness among the community. The main objective of this study is to assess the effect of HEBI on improving flood disaster preparedness among the community in Selangor. This study aims to develop, implement, and evaluate the impact of health education-based intervention (HEBI) based on knowledge, skills, and preparedness to improve flood disaster preparedness among the community in Selangor.

**Method:**

A single-blind cluster randomized controlled trial will conduct at six districts in Selangor. Randomly selected respondents who fulfilled the inclusion criteria will be invited to participate in the study. Health education module based on Health Believed Theory will be delivered via health talks and videos coordinated by liaison officers. Data at three-time points at baseline, immediate, and 3 months post-intervention will be collected. A validated questionnaire will assess participants’ background characteristics, knowledge, skill, and preparedness on disaster preparedness and perception towards disaster. Descriptive and inferential statistics will be applied for data analysis using IBM Statistical Package for Social Sciences version 25. Longitudinal correlated data on knowledge, skills, preparedness, and perception score at baseline, immediate post-intervention, and 6 months post-intervention will be analyzed using Generalized Estimating Equations (GEE).

**Discussion:**

It is expected that knowledge, skills, preparedness, and flood disaster perception score are more significant in the intervention group than the control group, indicating the Health Education Based Intervention (HEBI).

**Trial registration:**

Thai Clinical Trial TCTR20200202002.

## Background

The definition of a disaster is an event that can cause disturbance and disruption of social activity and nation’s business, loss of life, damage to property, economic loss or environmental destruction, which goes beyond the society’s capability to overcome it and requires an extensive pooling of resources [1]. At the same time, a flood can be defined as an excessive volume of water that can inundate a wide area or property.

Therefore, a flood is recognized as a natural disaster. The flood can be linked to several floods, such as beach floods, flash floods, river floods, underground floods, and sewage floods [2, 3]. Beach flood occurs when storms or extreme weather combined with a high tide causing sea level to rise above the average level, forcing seawater to overflow into the land. Heavy rainfalls cause a flash flood on an area, which collects a large volume of water rapidly. Due to an inadequate drainage system or waste or segregated material blockage [3].

On the other hand, flood disaster preparedness across communities is rarely discussed, either by individuals, health care providers, or the government, before complications occur. Certain groups are unaware that disadvantaged people, such as women, children, and the elderly, need special consideration in disaster preparedness [4]. As a result, it would benefit the community’s existing disaster preparedness if this intervention is successful.

Some theories explain behavior and suggest developing an effective way to influence behavior, such as Health Belief Model theory, Ecological theory, Social Cognitive Theory, Knowledge, Attitude and Preparedness theory, and Precaution Adoption Process Model theory. In these theories, researchers are provided with a guide to understanding people’s behavior toward health promotion and identifying information needed to design an effective strategy. Other than that, researchers are also guided to provide insight on how to create a successful program. On the other hand, interventions based on a theoretical foundation are more effective and result in a successful public health intervention program [5]. The function of theories is to understand why people chose to agree and refused to participate in healthy behavior.

One of the most established and oldest conceptual frameworks of health behavior is The Health Belief Model (HBM). This model is applied to disaster preparedness efforts, mainly focusing on human behavior [6]. Preparedness efforts focus on changing human behaviors to reduce people’s risk and increase their ability to cope with hazard consequences. Health Belief Model was developed by focusing on the attitudes and beliefs of individuals. There are four main pillars in the Health Belief Model that representing the perceived threat and net benefits. In addition, they have perceived susceptibility, perceived severity, perceived usefulness, and perceived barriers. This model was introduced as auditing for people’s readiness to act. Additionally, cues to action would activate that readiness and stimulate overt behavior. On the other hand, the self-efficacy concept of inefficiently performing is a recent addition to the Health Belief Model [7].

This study will provide a platform for increasing knowledge and promoting correct skills and preparedness toward flood disaster preparedness. This study will also contribute to the body of knowledge on the preparation of flood disasters among the community. This study aims to develop, implement, and evaluate health education-based intervention (HEBI) based on knowledge, skills, and preparedness as the primary outcome and changing of disaster perception (Perceived Benefit, Perceived Barrier, Self-Efficiency, Cues to action) as secondary outcome using the Health Believes Theory Model to improve flood disaster preparedness among the community. The conceptual framework as in Fig. 1.

**Fig. 1 Fig1:**
[figure not shown]
Conceptual framework using Health Belief Model on Flood Disaster Preparedness

## Methods

### Trial registration

Name: Thai Clinical TrialTrial Registration Number: TCTR20200202002Date of Registration: 02 February 2020Overall Recruitment Status: RecruitingStudy Start Date (First enrolment): 01 June 2020Completion Date (Last subject, Last visit): 31 May 2023Study Completion Date: 01 September 2023URL of Trial Registry Record: https://www.thaiclinicaltrials.org/show/TCTR20200202002

### Study design and study location

This study is a two-armed, parallel, single-blinded, cluster-randomized trial. The cluster in this study is defined as a district in Selangor. There are two groups which are the intervention group and the control group. Both groups follow a similar design until the end of the study. The clusters and participants are blinded for the study. The intervention group will receive HEBI, while the control group will receive a non-communicable health program.

Selangor is one of 13 states in Malaysia, located on the west coast of the Malaysian Peninsular. Selangor covers 7930 km2 [8], with a total population of 6.47 million reports to the Department of Information Malaysia, ranking it the most populous state in Malaysia (19.9%). It has a population growth rate, 1.4% and a high level of urbanization (91.4%) [8]. In addition, it has the largest economy in Malaysia in terms of gross domestic product (GDP) contribution, contributing 22.4% of the total Malaysian GDP [8]. The ethnic composition consists of Malay, 52.9%, Chinese, 27.8%, Indian, 13.3%, and other ethnic groups.

The study will carry out in six districts in Selangor state. First, those districts are chosen based on similar backgrounds related to the flood disaster. Then, those districts are ranked based on floods every year and the severity of the disaster using the Department of Irrigation and Drainage Malaysia data. Based on the rank, district Hulu Langat, Hulu Selangor, Kuala Selangor, Sepang, Sabak Bernam and Gombak were included in this study. Then those districts are divided into intervention groups and control groups using a coin toss. As for respondents, they were selected from each household in those districts based on eligibility.

### Study population and respondent selection

The sampling population is the communities from flood-prone areas in Selangor that fulfilled the inclusion and exclusion criteria. An individual from each household selected from Hulu Langat, Hulu Selangor, Kuala Selangor, Sepang, Sabak Bernam, and Gombak in Selangor state met the inclusion and exclusion criteria. The inclusion criteria are a citizen and individual age 18 years old and above, and the exclusion criteria are literate individuals and physically handicapped status.

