### Data collection method

The delivery of the intervention is design to address the limitations that occurred during the COVID-19 pandemic. The intervention and data collection will be carried out at the study site by liaison officers. The researcher can use the module and communicate with the liaison officers about the intervention’s flow and data collection. Respondents will give their consent through consent forms. Subsequently, respondents will be provided with a questionnaire to fill out, utilizing baseline data for the study (T0). Immediately upon completion of the health intervention, respondents will be provided with a questionnaire to respond to the immediate post-intervention assessment (T1). Knowledge, skills, and preparedness outcomes will be assessed at this stage. Six months after completing the health education intervention, respondents would be reassessed on the same effects as knowledge, skills, and preparedness (T2).

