### Intervention

The intervention arm will receive the Health Education Based Intervention module (HEBI) developed based on the Health Belief Model Theory as in Table 1, consisting of:
i.The two-hour educational talk will be conducted to all participants, including the importance and benefit of disaster preparedness, difficulties during the disaster, joint issues, and steps to success.ii.Educational disaster preparedness video in which the benefits of disaster preparedness will be introduced and demonstrated.iii.Booklets describing the importance of disaster preparedness, written, and published by the Ministry of Health Malaysia, were distributed. It contains practical during disaster and management of ordinary during disaster problem problems.iv.Brainstorming sessions with the researcher also provide for the community to overcome any individual problem.v.The community supports a disaster preparedness support group in which people can contact them personally by phone during the intervention program.

**Table 1 Tab1:** Summary of the Intervention Activities

Stage	HEBI Components	Theoretical Model Constructs	What and How It Is Delivered
Knowledge	i. Group education (health talk and group discussion) ii. Surrogate experimental learning (Brochure, flyer, poster, video)	i. Perceived Benefit ii. Perceived Barrier iii. Self-Efficiency iv. Perceived susceptibility	i. General knowledge about disaster preparedness will be assessed, and all material will be disseminated during the intervention. ii. Perceived benefit and perceived benefit were assessed during the discussion about the disaster preparedness barrier and the benefit of preparedness. iii. A baseline questionnaire will assess every individual before intervention is programmed. iv. The intention of the preparedness will be assessed.
Skills	i. Interactive learning with the community (brainstorming)	i. Cues to action	i. Information related to the advantage and disadvantages of preparedness. ii. Information about disaster preparedness was explaining. iii. Information on HEBI intervention how to prepare individuals for disaster.

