Respondents completed scales assessing “susceptibility”, “severity”, “benefits”, “barriers”, “self-efficacy” and “cues to action”. All items were scored on a five-point Likert scale from 1 (strongly disagree) to 5 (strongly agree). All subscales measured General Disaster Preparedness Belief (GDPB). Negatively worded statements (4,6,8,9,17-30,31,35,37,38,42,44) were used, the scores on the items were reverse-scored so that a higher score represented more positive disaster preparedness belief. Total score for each item for susceptibility (30), severity (20), benefits (30), barriers (70), self-efficacy (40), and cues to action (50). Responses were scored and categorized as high (75th quartile), moderate (75–25th quartiles), and low (25th quartile).

The GDPB score measured respondent’s positive disaster preparedness beliefs. It was computed by summing up the six subscales (Self Efficacy + Cues to action + Perceived susceptibility + Perceived low barrier (items were reverse scaled) + Perceived benefits + Perceived severity). Thus, it measured six dimensions with 45 items.

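### The exclusion criterion as written bars literate people, which contradicts the trial's own questionnaire, printed materials and written consent

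*Protocol article*

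**What the plan says.** Under 'Study population and respondent selection', the protocol article gives the whole eligibility rule in one sentence. "The inclusion criteria are a citizen and individual age 18 years old and above", and "the exclusion criteria are literate individuals and physically handicapped status". Literacy appears nowhere else in the rule, and no other section restates or corrects it.

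The procedures are described elsewhere:

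- 'Data collection method', baseline (T0): "respondents will be provided with a questionnaire to fill out".
- The same section, directly after the intervention: "respondents will be provided with a questionnaire to respond to the immediate post-intervention assessment (T1". At T2 the same outcomes are reassessed, with no mode stated.
- 'Outcome assessment', on the General Disaster Preparedness Belief scales: "Respondents completed scales assessing" the six belief domains, each item on a five-point Likert scale.
- 'Intervention': "Booklets describing the importance of disaster preparedness, written, and published by the Ministry of Health Malaysia, were distributed". Table 1 adds brochures, flyers and posters.
- 'Data collection method' and 'Ethical consideration': consent is given on consent forms and is written.

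**The concern.** Eligibility defines who the result is about. The stated aim concerns the community in Selangor, and the inclusion side of the rule is correspondingly broad. The exclusion side, as printed, removes every literate member of that community and keeps those least able to use a form they fill out themselves. The primary outcomes (knowledge, skills, preparedness) and the secondary outcome (disaster perception) all come from that questionnaire.

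Two things are at stake:

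- If the rule is followed, the trial recruits a population for which its measurement procedure is unsuitable.
- If the rule is silently reinterpreted, the trial recruits a population opposite to the one it reports. Anyone replicating the trial or abstracting it for a systematic review would then record the wrong population.

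**Working it through.** This is a check of wording, so the passages are set side by side.

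**Step 1. Who is eligible on the literal rule.** Included: citizens aged 18 or over. Removed: literate people and people with a physical handicap. Remaining: adult citizens who are not literate and not physically handicapped.

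**Step 2. What each procedure asks of that group.**

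| Procedure (section) | What the article describes | Does it need reading? |
|---|---|---|
| Baseline questionnaire ('Data collection method') | Respondent fills it out | Yes |
| T1 questionnaire (same section) | Given to the respondent to answer | Probably; mode not explicit |
| T2 reassessment (same section) | Same outcomes, mode not stated | Not determinable |
| Belief scales ('Outcome assessment') | Completed by respondents; 10 + 5 + 6 + 14 + 6 + 4 = 45 items | Yes, on the wording used |
| Knowledge, skills and preparedness items ('Outcome assessment') | Knowledge responses are prompted; skills and preparedness items are put to the respondent | Could be oral |
| Booklets, brochures, flyers ('Intervention', Table 1) | Printed matter | Yes |
| Talk, video, brainstorming, phone support, first-aid demonstration, field visit (same) | Spoken, visual or practical | No |
| Consent ('Data collection method', 'Ethical consideration') | Written, on forms | Yes, unless a separate route exists |
| Questionnaire validation ('Validity') | Translated into Bahasa Melayu; participants judge clarity and wording | Suggests readers |

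**Step 3. Is there any provision for non-readers?** The article describes no interviewer-administered version and no consent route for people who cannot read. A trial meant for non-literate adults would need both. The literal rule therefore conflicts with at least the baseline questionnaire, the belief scales, the printed materials and the consent procedure.

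**Step 4. Does any figure depend on it?** No. The sample size follows from its own inputs: 24 per arm, 2 × 24 = 48, 48 × [1 + (31 − 1) × 0.005] = 55.2, and 55.2 / 0.66 = 83.6, rounded up to 84. No term involves literacy, so correcting the criterion leaves 84 unchanged.

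**Step 5. Is the question still live?** 'Trial registration' gives the status as recruiting, with first enrolment on 1 June 2020. The article was published on 24 September 2021. On those dates people may already have been screened under whichever rule was in use.

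**The case against.** The strongest reply is that this is a language slip. The article has others, such as calling intention to treat the purpose to treat concept, and naming perceived benefit twice in one line of Table 1. A screener applying the rule literally would have to turn readers away and then hand a form to people who cannot read it, which is unlikely to have happened. The full protocol and screening form are not shown and may be correct.

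Much of this stands. A slip is the most probable explanation, and nothing shows that the wrong people were enrolled. But the sentence is the eligibility rule itself, and the article offers nothing that overrides it.

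Some stronger readings are tempting, and the documents do not support them:

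- **That every outcome is self-completed at all three visits.** Filling out is stated only for T0. The description of the knowledge, skills and preparedness items leaves some room for oral administration. Self-completion is the likelier reading, not a uniform fact.
- **That the intervention depends on reading.** Several components do not.
- **That the rule shuts out nearly the whole population.** No literacy rate is given, so no share can be claimed.
- **That liaison officers will screen differently by district and so unbalance the arms.** The article gives them the intervention and data collection and does not say who judges eligibility. Districts are allocated first and eligible people are invited afterwards, with three districts per arm. An ambiguous rule could therefore be applied unevenly, but this is a possible risk that nothing in the article demonstrates.

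**Conclusion.** The point holds as a contradiction between the eligibility rule and the procedures. The exclusion of literate people cannot be squared with a baseline questionnaire that respondents fill out, scales that they complete, printed intervention material and written consent, when no provision for non-readers is described. It needs correcting even though it is probably a slip, because read literally it excludes the people able to use the self-completed measures and reverses the population to which the result applies.

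The size is qualitative: one operative criterion is stated in reverse, and no numerical result is affected. The conclusion assumes that the article's wording reflects the rule in use. If the full protocol already says illiterate, only the published text needs correcting.

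**What to change.** 1. Confirm the intended rule and correct 'Study population and respondent selection'. If the word is a slip, the exclusion should read illiterate individuals. If non-readers were really intended, keep the rule and reconcile 'Data collection method', 'Outcome assessment' and 'Ethical consideration' by stating oral administration and a consent route for people who cannot read.
2. Do not turn the correction into a new, narrower criterion such as inability to read Bahasa Melayu. 'Study design and study location' puts the state at 27.8% Chinese and 13.3% Indian, and a person literate in another language is not illiterate.
3. Use the same screening wording in all six districts.
4. Confirm which rule was applied to people already enrolled, and report it.

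The text correction is one word. Confirming past screening is a modest check of existing records. The sample size and analysis do not change.

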### Sample size estimation

The sample size (N) for this study was calculated by comparing the populations of two groups when the endpoint is quantitative. Using the formula by Lameshow and Lwanga (1990):
$$ N=\frac{{\left[{\mathrm{Z}}_{1-\sigma /2}\surd 2\mathrm{P}\left(1-\mathrm{P}\right)+{\mathrm{Z}}_{1-\beta}\surd {\mathrm{P}}_1\left(1-\mathrm{P}\right)+{\mathrm{P}}_2\left(1-{\mathrm{P}}_2\right)\right]}^2}{{\left({P}_1-{P}_2\right)}^2} $$

Where,

N = Sample size estimation

Z_1− σ/2_ = Standard error associated with 95% confidence interval 1.96

Z_1− β_ = Standard error associated with 80% power = 0.842

P_1 =_ Population proportion 1

P_2_ = Population proportion 2

P = P_1 +_ P_2_ / 2

Thus, the calculation below is based on study flood preparedness [9]:

The proportion of follow-up for flood preparedness in the intervention group.

P_1_ = 79.6% = 0.79.

Proportion of follow-up for flood preparedness in control group.
$$ {\mathrm{P}}_2=40.2\%=0.40 $$$$ \mathrm{P}={\mathrm{P}}_{1+}{\mathrm{P}}_{2/}2=\left(0.79+0.40\right)/2=0.59 $$$$ N=\frac{{\left[1.96\surd 2(0.59)\left(1-0.59\right)+0.84\surd 0.79\left(1-0.79\right)+0.40\left(1-0.40\right)\right]}^2}{{\left(0.79-0.40\right)}^2} $$$$ N=3.53/0.15 $$$$ N=24 $$

Taking into account comparison 2 groups.
$$ N=48 $$

Taking into account the design effect = 48 x [1 + (m-1) ICC].

Where m = average cluster size, ICC = intracluster correlation coefficient.

m = 31 [10], ICC = 0.005 based on adjusted ICC for individual- and cluster-level characteristics [10].

Thus, 48 × [1 + (31 – 1)0.005] = 55.2

Adjusting 34% attrition rate [11].

55.2 / 0.66 = 84 final sample sizes estimated for both intervention and control group.

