### Sampling method and subject recruitment

Randomization of the participants will conduct based on the district they belong to. The six districts chosen earlier were randomly assigned into the intervention and control groups with 1:1 allocation. Thus, three districts belong to the intervention group, and three are used in the control group. Figure 2 shows the procedures involved in the recruitment of subjects in this study.

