## Data analysis

### Data entry and analysis

Respondents’ responses to distributed questions will be used to enter data. The research assistant will document the response into IBM SPSS Version 25 (Statistical Package for Social Sciences). Before the final review, data cleaning will be performed to look for any missing data or outliers. Then, the data will be translated to long-form for analysis using the Generalized Estimating Equation (GEE). Descriptive and inferential statistics will be used to analyze the data. In descriptive statistics, continuous data will be reported in either a mean with standard deviations or a median with an interquartile range. Categorical data will be represented in percentages, while continuous data will be reported in either a mean with standard deviations or a median with an interquartile range. The histogram, skewness over the standard error of skewness, and statistical tests of Kolmogorov-Smirnov and Shapiro-Wilk normality tests will be used to screen for normality. If the normality test conditions are met, parametric tests will be used to continue the analysis; otherwise, non-parametric equivalents will be used. A significant alpha level of 0.05 will be used for inferential analysis, and *P*-values will be stated as two-sided.

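### The 80% power behind the target of 84 ignores that only six districts are randomised; on the article's own inputs, an unadjusted comparison on 4 degrees of freedom has about 62–66%

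*Protocol article*

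**What the plan says.** All places are in the protocol article.

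- **Sample size estimation** compares two proportions, 0.79 v 0.40, using 1.96 for the two-sided 5% level and, for power, "Standard error associated with 80% power = 0.842".
- That gives 24 per group and 48 in total. The design effect follows, with "m = 31 [10], ICC = 0.005 based on adjusted ICC for individual- and cluster-level characteristics [10", so that "Thus, 48 × [1 + (31 – 1)0.005] = 55.2".
- Attrition of 34% is then allowed for: "55.2 / 0.66 = 84 final sample sizes estimated for both intervention and control group".
- **Study design and study location** defines the cluster as a district. **Sampling method and subject recruitment** states: "The six districts chosen earlier were randomly assigned into the intervention and control groups with 1:1 allocation", that is, three districts per arm.
- **Data entry and analysis** sets the test level: "A significant alpha level of 0.05 will be used for inferential analysis, and *P*-values will be stated as two-sided".
- **Generalized estimating equation (GEE)** plans a covariate-adjusted longitudinal GEE. The article names no small-sample method.

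**The concern.** The design effect corrects the variance for clustering, but it does not account for how few clusters there are. With three districts per arm, the between-district variation that the treatment contrast must be judged against is estimated from six units. At the 5% level the critical value is then 2.776 (t on 4 degrees of freedom), not 1.96. A calculation that uses 1.96 and 0.842 and never mentions six districts would give the same answer for 6 clusters or 60.

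Two inputs also come from another study. The cluster size of 31 does not fit a total of 84 over six districts. The ICC is a value left after adjustment for individual- and cluster-level characteristics, and six districts leave little room for adjusting at cluster level.

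At stake is how the result will be read. A null finding would be taken as coming from a trial with a one-in-five chance of missing a 39-point effect. If the chance is nearer one in three, the finding says less than readers will suppose.

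**Working it through.** **1. The article's own figure**

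- Numerator: [1.96·√(2 × 0.59 × 0.41) + 0.84·√(0.79 × 0.21 + 0.40 × 0.60)]² = 3.60 (the article prints 3.53).
- Denominator: 0.39² = 0.152 (the article prints 0.15).
- 3.60/0.152 = 23.7, so 24 per arm and 48 in total. The article's 3.53/0.15 = 23.5 also rounds to 24.
- 48 × 1.15 = 55.2, and 55.2/0.66 = 83.6, so 84.

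The figure reproduces. Since 48 is already the two-arm total, 84 is a total and not a per-arm number.

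**2. Power with six districts**

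Inputs from the article: 0.79 v 0.40, ICC 0.005, 34% attrition, two-sided 5%, three districts per arm. Assumption: respondents are spread evenly over districts.

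- Analysed: 84 × 0.66 = 55.4, which is 27.7 per arm and 9.24 per district.
- Design effect: 1 + 8.24 × 0.005 = 1.041.
- SE = √[(0.79 × 0.21 + 0.40 × 0.60) × 1.041/27.72] = √(0.4059 × 1.041/27.72) = 0.1235.
- Non-centrality: 0.39/0.1235 = 3.16.
- Non-central t on 4 degrees of freedom, critical value 2.776: **power 66%**.
- Check by beta-binomial simulation (200,000 runs, 9 per district, t-test on the six district proportions): **62.5%**.

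**3. Where the loss comes from**

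| Setting (55.4 analysed) | Power, normal quantiles | Power, t on 4 df |
|---|---|---|
| Article's design effect, m = 31 (1.15) | 80.8% | 62% |
| m = 14 (design effect 1.065) | 83.8% | 65% |
| m = 9.24 (design effect 1.041) | 84.7% | 66% |
| ICC = 0 | 86% | 68% |

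Moving from normal quantiles to 4 degrees of freedom costs about 18 points in every row. Replacing 31 by the trial's own cluster size raises power.

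**4. The cluster size**

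84/6 = 14 recruited per district, whereas 6 × 31 = 186. With m = 14 the article's formula needs 48 × 1.065/0.66 = 77.5 respondents, fewer than 84.

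**5. Sensitivity to the ICC and to attrition**

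ICCs above 0.005 are assumptions. Each range runs from the simulation to the non-central t.

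| ICC | About 55 analysed | All 84 analysed |
|---|---|---|
| 0.005 | 62–66% | about 80–82% |
| 0.02 | 58–62% | 73–75% |
| 0.05 | 51–54% | 63–64% |
| 0.10 | 43–44% | about 51% |

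**6. Detectable difference**

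From 40% in control, with 55.4 analysed and 80% power by non-central t on 4 degrees of freedom: about 44 points at ICC 0.005 and 49 points at ICC 0.05. The article assumes 39.

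**The case against.** The strongest reply is that 62–66% belongs to a simpler analysis than the one planned. The article plans a covariate-adjusted GEE over three time points, and the outcomes are scored on scales. With 4 degrees of freedom, about 55 analysed and ICC 0.005, multiplying the variance by 1 − r² for an assumed baseline correlation r gives about 78% power at r = 0.5 and 83% at r = 0.6. The primary outcomes are also measured immediately after the intervention, when attrition may be small; with all 84 analysed, power is about 80–82%. Finally, a small-sample correction for GEE is commonly left to the full analysis plan.

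Much of this stands as a limit on the claim. It is not shown that every valid analysis of this trial falls short of 80%. But the power statement rests on an unadjusted two-proportion comparison after 34% loss, gives no baseline correlation, and must be judged on those terms. GEE does not add clusters either: referring a 4-degree-of-freedom t statistic to 1.96 would keep the power but give a type I error of about 12%, not the stated 5%. The point is not that a correction goes unnamed; it is that the stated sample-size calculation leaves out the number of clusters.

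Two stronger readings are tempting and are not supported:

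- *A reader might infer that m = 31 costs power.* It does the opposite: it makes the design effect too large.
- *A reader might infer that the true ICC is well above 0.005 and power is therefore near 50%.* The article gives no unadjusted ICC, plans covariate adjustment, and chose districts with similar flood backgrounds. With normal quantiles and about 9 per district, power stays at or above 80% up to an ICC of about 0.02, so the ICC alone does not establish a shortfall.

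**Conclusion.** The concern holds in a limited form. The 80% is not a property of a design with three districts per arm. For the comparison the article itself sizes, power is about 62–66% at ICC 0.005 and at most 68% at ICC 0, so the shortfall does not depend on a disputed ICC. Its cause is the use of normal quantiles where only 4 between-district degrees of freedom exist.

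This rests on 34% attrition at the analysed time point, an even spread over districts, no gain from baseline adjustment, and a test that holds the 5% level. Relaxing the attrition or the no-gain assumption could bring power to about 80%; a larger ICC would take it lower, by an amount the article does not allow one to fix.

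The cluster size of 31 is a separate and conservative inconsistency. The chain of arithmetic from 24 to 84 is sound as far as it goes.

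**What to change.** Keep the recruitment target and rewrite the justification under Sample size estimation:

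- State six districts, three per arm, and a t reference on 4 degrees of freedom.
- Replace 31 by the trial's own cluster size: 14 recruited and about 9 analysed per district, if evenly spread.
- Give power as about 62–66% at ICC 0.005 for an unadjusted comparison after 34% attrition, and about 80–82% if all 84 are analysed.
- Say that 0.005 is a covariate-adjusted ICC, and add a table over larger ICCs (for example 0.02, 0.05 and 0.10), labelled as assumptions.
- Give the detectable difference: about 44–49 points from 40% in control, for ICC 0.005 to 0.05.
- If credit is claimed for baseline adjustment, state the assumed correlation and its source.
- Drop the unqualified 80% claim.

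The cost is one rewritten paragraph and a less favourable stated power, with no extra respondents. This corrects the statement and does not restore 80%. With six districts and ICC 0.005, 80% would need about 81 analysed, or 81/0.66 = about 123 recruited; more districts would be the sounder route if the sponsor wants the power itself.
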